
On the other hand, in Chile, more than 70% of people over the age of 60 years old are classified as physically inactive [18], with women having the highest prevalence at 74.2%, and men at 54.7% [18]. Additionally, Chilean women are more sedentary (90%) and have a higher prevalence of overweight/obesity (74.8%) than men, who reach 83.3% and 73.6% for the same variables, respectively [19]. These data represent elements that would have a negative impact on the health status of Chilean older women [20]. Therefore, this study protocol aims to analyze and compare the effects of an adapted taekwondo program with respect to multi-component training and walking exercise on health status (blood pressure, lipid profile, frequency of food consumption, body composition, cognitive status, brain activity, health-related quality of life and physical-functional fitness) in independent older women. Secondarily, analyze the variability of the inter-individual response of the participants and compare according to the designated training system.

Based on previous studies [6,7,8,9,11,12,14,15,16,17] we hypothesized that: (i) adapted taekwondo produces significantly greater effects on cognitive status, brain activity, health-related quality of life, and postural balance than a multi-component training and walking exercise, and; (ii) older women who participate in the adapted taekwondo program have more favorable inter-individual responses (higher percentage of responders) in cognitive status, brain activity, health-related quality of life and postural balance compared to women who participate in a multi-component training and walking exercise.

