#### 2.6.4. Control Group (CG)

Regarding the CG, the individuals will participate in the assessments (initial and final) and will be asked to maintain their usual activities of daily living. A research assistant will contact the participants by telephone (once a week) to inquire about their health status and monitor their activities. At the end of the intervention period, the CG will be invited to participate in a physical activity program developed at the University based on the results of this study.

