### 2.7. Outcomes and Procedures

The first meeting with the participants will be held to explain the scope and aim of the study, obtain the signature of informed consent, administer the anamnesis, and randomly assign them to the intervention groups. Next, for a week, the older women will be assessed on the variables considered for the study; later, they will participate in the designated training programs. After 16-weeks of intervention, older women will undergo the same initial assessments for one week. One of the researchers will supervise all the assessments, which will be carried out by an anthropometrist (body composition), a nurse (blood pressure, lipid profile, and frequency of food consumption), a speech-language pathologist (cognitive status and health-related quality of life), a psychologist specializing in neuroscience (brain activity), and two physical education teachers (physical-functional fitness). The evaluators will not have information about the training groups, nor will the participants know their identities (i.e., a double-blind shield). Figure 2 shows a summary of the assessments and sessions that are usually part of the intervention.

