#### 2.8.1. Intention-to-Treat Analysis

A two-factor repeated measures ANOVA will be used to determine the effects of the intervention on the outcomes (group × time). Post-hoc tests will be performed with an alpha adjusted by Bonferroni to identify statistically significant differences. The effect sizes will be calculated utilizing Cohen’s d [35] within the group and between the groups, using the following equation: effect sizes = (post mean − pre mean)/standard deviation combined. The level of significance will be set at 5%. The intraclass correlation coefficient will be used to verify the measurement’s reliability, with a predetermined threshold of 0.80 being used to include the data in the analyses. The inter-individual variability of the intervention will be determined using previously reported criteria, and responders and non-responders will be classified using the technical error (TE) of measurement. This TE will be calculated according to the formula: TE = SD (standard deviation) dif/√2, where SD is the variance of the differences in the observed values of two repeated measurements in each test [36]. A non-responder is a person who does not show an increase or decrease (in favor of beneficial changes) in the study variable greater than twice the TE, far from zero. Thus, a shift in favor of beneficial health effects, which is <2 TE means the existence of a high probability (12 to 1 odds ratio) that the response to exercise is true [36,37]. In addition, Fisher’s exact test will compare groups of participants who were at 2 × TE calculated on each outcome as non-responders and more than twice the TE as responders [37].

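### Section 2.8.1 lets an ICC of 0.80, apparently estimated in the trial, decide which data enter the intention-to-treat analysis

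*Protocol article*

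**What the plan says.** Section 2.8.1 of the protocol article gives the ICC a gatekeeping role, "with a predetermined threshold of 0.80 being used to include the data in the analyses". It does not give the form of the ICC, the measurements it is computed from, or whether a value below 0.80 removes an outcome, a test or some women's values. Section 2.8.2 applies the same procedures to the per-protocol analysis, so the rule carries over.

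The schedule in section 2.7 has one assessment week before training ("Next, for a week, the older women will be assessed on the variables considered for the study") and one after ("After 16-weeks of intervention, older women will undergo the same initial assessments for one week"). Section 2.6.4 likewise gives the control group two assessments. The technical error in section 2.8.1 presupposes a repeat of every test: "where SD is the variance of the differences in the observed values of two repeated measurements in each test". The schedule does not place those repeats.

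The outcomes with most at stake are those in the hypothesis (section 1): "adapted taekwondo produces significantly greater effects on cognitive status, brain activity, health-related quality of life, and postural balance" than the two comparison programmes.

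**The concern.** An inclusion rule applied to an estimate makes the content of the analysis depend on sampling error. An outcome named in the hypothesis could fall below the cut-off by chance and not be analysed. If the rule acts on values rather than whole outcomes, randomised women would lose data under an intention-to-treat heading.

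The rule gains little in return. For a randomised comparison of means, measurement error of the same kind in every arm widens the interval but does not bias the difference. The responder analysis already allows for error through its two-technical-error criterion.

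A further risk depends on where the repeats come from. If the only two values per woman were those before and after 16 weeks, the ICC would mix measurement error with change. Outcomes that change would then look unreliable.

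**Working it through.** The plan gives no ICC value, so there is no figure of its own to reproduce.

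**Inputs from the article.** Threshold 0.80 (2.8.1). Four arms of 16, 64 women in total (2.4). Chair stand difference 3.46 with SD 3.38 (2.3).

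**Assumptions.** Normal data, two measurements per woman, true reliability ρ of 0.80 to 0.95, and the shift patterns given below in SD units.

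**Step 1: where repeats are described.**

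| Outcome | Repeat described within an assessment |
|---|---|
| Blood pressure (2.7.1) | Two readings, a third if they differ by more than 5 mmHg |
| Handgrip (2.7.1) | Three attempts per hand |
| Cognitive status, brain activity, quality of life | None |
| Postural balance | One 30 s recording with eyes open and one with eyes closed; no repeat of either |

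**Step 2: chance exclusion with genuine repeats.** For two measurements in n women, with mean squares for rows (women, MSR), columns (occasions, MSC) and error (MSE):

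- agreement ICC = (MSR − MSE) / (MSR + MSE + 2(MSC − MSE)/n)
- consistency ICC = (MSR − MSE) / (MSR + MSE)

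Simulation with n = 64 gives P(ICC < 0.80) of about 50% at ρ = 0.80, 10–11% at 0.85 and about 0.2% or less at 0.90.

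A check by Fisher's transformation, z = ½ ln[(1+ρ)/(1−ρ)] with standard error 1/√(64 − 1.5) = 0.1265:

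- ρ = 0.85: (1.2562 − 1.0986)/0.1265 = 1.25, so 10.6%
- ρ = 0.90: (1.4722 − 1.0986)/0.1265 = 2.95, so 0.16%

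**Step 3: if pre and post values feed the ICC.** Let δ be the shift in each arm. In large samples:

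- agreement ICC = ρ / (1 + mean(δ²)/2)
- consistency ICC = ρ / (1 + var(δ)/2)

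For ρ = 0.90 and shifts 1, 0.5, 0.5, 0:

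- mean(δ²) = (1 + 0.25 + 0.25 + 0)/4 = 0.375, so agreement = 0.90/1.1875 = 0.76
- mean(δ) = 0.5, so var(δ) = 0.375 − 0.25 = 0.125 and consistency = 0.90/1.0625 = 0.85

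A shift of 0.5 in every arm, with no difference between arms, already gives agreement = 0.90/(1 + 0.25/2) = 0.80. Most of the fall therefore comes from the average change over time. Differences between arms account only for the step from 0.80 to 0.76.

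For the protocol's own difference in all three trained arms, δ = 3.46/3.38 = 1.024:

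- mean(δ²) = 3 × 1.048/4 = 0.786, so agreement = 0.90/1.393 = 0.65
- var(δ) = 0.786 − 0.768² = 0.196, so consistency = 0.90/1.098 = 0.82

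Simulated exclusion at ρ = 0.90, with 16 women per arm:

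| Shifts (SD) | Agreement | Consistency |
|---|---|---|
| none | 0.2% | 0.2% |
| 0.5 / 0.25 / 0.25 / 0 | about 6% | about 1% |
| 0.5 / 0.5 / 0.5 / 0 | 29% | 1.6% |
| 1 / 0.5 / 0.5 / 0 | about 86% | 12% |
| 1.02 / 1.02 / 1.02 / 0 | 100% | 33% |

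The last pattern gives 100% and 74% at ρ = 0.85, and 100% and 4% at ρ = 0.95.

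**The case against.** The strongest reply is that verifying reliability ordinarily means repeating a measurement under unchanged conditions. On that view the pre-post reading is the least natural one. The technical-error formula speaks of two repeated measurements in each test, blood pressure and handgrip have within-session repeats, and a full week per assessment leaves room for more. A condensed article need not timetable them. With genuine repeats, exclusion does not depend on the training effect.

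This stands. A reader might infer that the trial has no repeat testing, or that the rule will remove the outcomes that respond most to training. The documents support neither. The second follows only if pre and post values feed the ICC, and its size then varies widely with the shifts, the reliability and the form of the ICC.

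The unit of exclusion is also open. The data could mean single recordings rather than whole outcomes, so it cannot be said that a hypothesised outcome would disappear. Discarding randomised women's recordings by a reliability result would still be selection made after the data are seen.

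Finally, the 50% figure arises only when the true ICC sits on the threshold, as with any cut-off, and at 0.90 chance exclusion is negligible. That is correct, but the article gives no ICC for any outcome, so a value near 0.80 or 0.85 cannot be ruled out.

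**Conclusion.** The concern holds as a data-dependent inclusion rule whose source, form and unit are unstated. It is a rule that the article states, not a detail left to a fuller document.

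Chance exclusion in 64 women is about 50%, 10–11% and 0.2% at true ICCs of 0.80, 0.85 and 0.90. This assumes that the ICC is estimated in the trial from two measurements per woman. The article names no outside source, so that is the natural reading, but it is not stated.

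Selection against responsive outcomes is a conditional risk only. It requires a pre-post ICC, and at an assumed reliability of 0.90 it runs from about 6% to 86% (agreement) or 1% to 12% (consistency) over the shift patterns 0.5/0.25/0.25/0 to 1/0.5/0.5/0 SD. It is higher still if all three trained arms gain the 3.46 repetitions used in the sample size calculation.

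**What to change.** In section 2.8.1, delete the clause that makes inclusion depend on the ICC. State instead that every pre-specified outcome is analysed for all randomised women whatever its ICC, and that the ICC and technical error are reported as a description of measurement quality. Add that both are estimated only from repeats within one assessment period, never from pre-post values.

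This is right whichever source of repeats was intended. It costs about one sentence; the only downside is that some noisier outcomes will be reported with wide intervals.

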## 4. Conclusions

This study protocol will analyze and compare the effects of a TKD program with respect to MCT and WE on health status in independent older women. Secondly, it will analyze the variability of the inter-individual response of the participants and compare them according to the designated training system. Our hypothesis indicates that TKD produces more significant effects and greater inter-individual responses (higher percentage of responders) in cognitive status, brain activity, health-related quality of life, and postural balance than MCT and WE. If this intervention proves to be beneficial, it might be included in public and private physical activity programs for older women.

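### The secondary aim is to compare variability of individual response, but the stated analysis compares responder percentages, which mix mean change with spread and cannot show whether variability differs

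*Protocol article*

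**What the plan says.** The Introduction (section 1) gives the secondary aim: "Secondarily, analyze the variability of the inter-individual response of the participants and compare according to the designated training system". The Abstract states the same aim, and the Conclusions (section 4) repeat it: "it will analyze the variability of the inter-individual response of the participants and compare them according to the designated training system".

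Hypothesis (ii) in the Introduction puts it differently. It expects that women in the taekwondo arm "have more favorable inter-individual responses (higher percentage of responders) in cognitive status, brain activity, health-related quality of life and postural balance" compared with the other two training arms.

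Section 2.8.1 gives the method: "The inter-individual variability of the intervention will be determined using previously reported criteria, and responders and non-responders will be classified using the technical error" of measurement, defined as "TE = SD (standard deviation) dif/√2". A non-responder is a woman without a beneficial change "in the study variable greater than twice the TE, far from zero". The between-group analysis is that "Fisher’s exact test will compare groups of participants who were at 2 × TE calculated on each outcome as non-responders", with those beyond the cut-off as responders.

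No comparison of the spread of change scores is described, either between training arms or against control. Levene's test appears in section 2.8, next to Shapiro-Wilk, as a check on the variables. It is not assigned to change scores or to the secondary aim. The control group is assessed at start and end (section 2.6.4), but no use of its SD of change is described.

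**The concern.** The aim names variability, and section 2.8.1 says that variability is what the responder split will determine. The null hypothesis of Fisher's test, however, is that the share of women above a fixed cut-off is the same in both arms. That share depends on where an arm's mean change lies relative to 2 x TE as well as on how widely the women differ. An arm in which every woman truly gains the same amount has more responders if that common gain is larger. Two arms with very different spread have the same share if both means lie at 2 x TE.

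Two misreadings could follow. A significant result could be reported as a difference in inter-individual response when it only repeats the mean difference already tested under hypothesis (i), for the same outcomes and arms. A non-significant result could be read as similar variability. Neither depends on single women being misclassified: both remain if every TE and every classification is right.

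**Working it through.** **The plan's own figure.** With TE = SD of differences/√2, a change that is pure measurement error has SD √2 x TE. With no true change, P(change > 2 TE) = 1 − Φ(2/√2) = 0.0786. The odds are 0.9214/0.0786 = 11.7 to 1, which reproduces the stated "a high probability (12 to 1 odds ratio) that the response to exercise is true". The cut-off is therefore understood correctly here.

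**Inputs from the protocol.** 16 women per group and 15% loss (section 2.3; 16 x 0.85 = 13.6, so 13 completers); 5% significance and an ICC threshold of 0.80 (section 2.8.1); 3.46 and 3.38 repetitions (section 2.3; 3.46/3.38 = 1.02).

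**Assumptions.** Normal changes; pairwise two-sided Fisher tests; scores in units of the between-woman SD. The protocol gives no TE, so it is derived from the ICC threshold: TE = √(1 − 0.80) = 0.447, 2 TE = 0.894, error SD of change = 0.447 x √2 = 0.632.

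**Formula.** P(responder) = Φ((mean change − 2 TE)/SD of change), where SD of change = √(2 TE² + SD of true response²). Fisher rejection rates are exact sums over all 2 x 2 tables. Brown-Forsythe rates are simulated.

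**A. No individual differences in true response in either arm; only the means differ.** The comparator gains 0.3 SD, so its responder share is Φ((0.3 − 0.894)/0.632) = 17%.

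| Mean difference (SD) | Responders, other arm | Fisher rejects, 16 per arm |
|---|---|---|
| 0.2 | 27% | 4% |
| 0.3 | 32% | 8% |
| 0.5 | 44% | 23% |
| 0.8 | 63% | 64% |
| 1.02 | 75% | 88% |

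With 13 per arm the last row becomes 84%. With ICC 0.90 and 16 per arm it becomes 99%.

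**B. Variability truly differs; the means are equal.** True-response SD is 0 v 1.0, so the SD of change is 0.632 v √(0.4 + 1.0) = 1.183.

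| Common mean | Responders | Fisher rejects, 16 per arm |
|---|---|---|
| 0 | 8% v 22% | 9.5% |
| 1 TE | 24% v 35% | 5% |
| 2 TE | 50% v 50% | 2% |
| 3 TE | 76% v 65% | 5% |

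A Brown-Forsythe test on the same change scores rejects in 48% to 49%, whatever the mean. Its size with equal spread is about 3.6%. With 13 per arm and both means at 2 TE, Fisher rejects in 3% and Brown-Forsythe in about 35%. With ICC 0.90 and 16 per arm, the figures at that mean are 2% and about 79%.

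**C. Limits of the alternative.** For a true-response SD of 0 v 0.5 at ICC 0.80, Brown-Forsythe power is only about 10% with 16 per arm and 7% with 13. If both arms vary (0.5 v 0.8), it is about 10% with 16 per arm.

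**The case against.** The best defence is that the protocol defines its own term. Hypothesis (ii) and the Conclusions gloss individual response as the percentage of responders, and the Discussion as responders against non-responders. Read that way, Fisher's test answers the question asked. This stands for hypothesis (ii). It does not settle the aim, because the Abstract, Introduction and Conclusions all say variability and section 2.8.1 says the responder split determines variability.

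A reader might take scenario A as an inflated false-positive rate. It is not: with 17% v 75% responders, equal proportions is false and rejecting it is correct. The figures show only that rejection is no evidence about variability. They are also small when the arms differ little (4% to 8% at 0.2 to 0.3 SD). The 1.02 is an illustration: it comes from the chair stand, which is not a hypothesis (ii) outcome, and may be a within-group effect. The 16 per group reproduces as a paired calculation (12.1, rounded up to 13; 13/0.85 = 15.3, rounded up to 16).

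A reader might also infer that Fisher's test here tests only a shift in mean. That is too strong. Spread alone moves the percentage unless the mean lies at 2 x TE, which is why Fisher reaches 9.5% at a mean of zero in scenario B.

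Finally, the criteria are cited to earlier publications and the full analysis plan is not shown. But section 2.8.1 spells out the cut-off, the TE formula and the test, so this is a stated method and not an omitted detail.

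**Conclusion.** The point holds as a mismatch between the stated secondary aim and the quantity analysed. Fisher's test on the share beyond 2 x TE is suitable for hypothesis (ii), but it cannot separate spread from mean change. Under normal changes, ICC 0.80 and 16 per arm, it rejects in 4% to 88% of trials as the mean difference goes from 0.2 to 1.02 SD with no individual differences in true response. It rejects in only 2% to 10% when true-response SD is 0 v 1.0 and the means are equal. The sizes depend on the assumed TE and means; the inability to separate the two components does not.

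The documents do not support the stronger conclusion that the response analysis is invalid or that the secondary question has no answer. As a comparison of responder percentages it can be carried out as written. The issue concerns a secondary aim and how its result will be described, and it should be corrected before analysis.

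**What to change.** In section 2.8.1, answer the variability aim on the continuous change scores:

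- For each outcome, report the SD of change by arm.
- Report the SD of individual response of each training arm relative to control, from SD_training² − SD_control², as an estimate with 95% CI. Where the difference is negative, report the signed variance difference and take no square root.
- Give a Brown-Forsythe comparison of change scores between training arms as supportive only.
- Keep Fisher's test for hypothesis (ii), labelled as comparing the proportion whose change exceeds measurement error. State that it depends on the mean and is not evidence of differing variability.

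At minimum, reword the aim and the Conclusions as a comparison of responder percentages and drop the reference to variability.

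The cost is a few lines of analysis text and output from data already planned in all four arms, with no new measurement or participant. The minimum option is wording only. The downside is imprecision: with 13 to 16 women per arm the confidence intervals will be wide and Brown-Forsythe has about 7% to 11% power for a response SD of 0 v 0.5 at ICC 0.80. The plan should therefore say that a non-significant result is not to be read as similar variability.

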**Abstract:**

This study protocol aims to analyze and compare the effects of an adapted taekwondo program with respect to multi-component training and walking exercise on health status in independent older women. Secondarily, we analyze the variability of the inter-individual response and compare it according to the designated training system. The sample will consist of 64 women between 60 and 65 years, randomly assigned to experimental group 1 (*n* = 16; adapted taekwondo), experimental group 2 (*n* = 16; multi-component training), experimental group 3 (*n* = 16, walking exercise) or control group (*n* = 16; no intervention). The experimental groups will perform the designated training for three sessions (60 min per session) per week over 16-weeks, while the control group will not receive any treatment. The main outcome will provide information about (i) blood pressure, (ii) lipid profile, (iii) frequency of food consumption, (iv) body composition, (v) cognitive status, (vi) brain activity, (vii) health-related quality of life (HRQoL) and (viii) physical-functional fitness. Our hypothesis indicates that adapted taekwondo produces more significant effects and greater inter-individual responses in cognitive status, brain activity, HRQoL, and postural balance than the others training methods. If this intervention proves effective, it could be an alternative for older women.

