## 3. Discussion

Despite being considered a risky activity [38], TKD has recently reported favorable physical, physiological, and psychoemotional responses in older people [9,15,16,17]. Previous studies have found that after 12-weeks of TKD and WE, participants had a considerably better response on static balance than a control group, with no differences between TKD and WE [39]. While one case study found that a TKD intervention reduced the chance of falls and the fear of falling in a 97-year-old man, the author adds that the evidence on the benefit proportionality of TKD in comparison to regularly used physiotherapy therapies is still unclear [40]. In this regard, conducting a study comparing the group and inter-individual responses (responders vs. non-responders) in older women subjected to a TKD program to other physical activity strategies adapted to the characteristics of older people (e.g., MCT and WE) could support the use of TKD as an efficient and safe activity for older women without putting their health at risk.

On the other hand, it is typical for interventions with young taekwondo practitioners to be of short duration (i.e., 4-weeks) using high-intensity interval training with specific techniques and an emphasis on improving physical performance [41,42,43,44]. These interventions cannot be extrapolated to older people, since the international physical activity recommendations suggest regular moderate to vigorous-intensity activities with emphasis on resistance training [3,5], which favors functional independence [4]. In addition, young taekwondo practitioners are generally athletes of regional or national level [41,42,43,44]. Therefore, the aim of the interventions does not seek to favor the health of the participants but rather the sports performance, instead, the older people generally practice physical activity to improve their health status [4,22].

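### Section 2.8.1 says variability of response is determined by the share of women beyond 2 × TE; that share tests hypothesis (ii) but mixes mean change with spread and does not identify variability

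*Protocol article*

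**What the plan says.** The Abstract gives the secondary aim: "Secondarily, we analyze the variability of the inter-individual response and compare it according to the designated training system". The Introduction repeats it ("Secondarily, analyze the variability of the inter-individual response of the participants and compare according to the designated training system"), and the Simple Summary and Conclusions word it in the same terms.

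The hypothesis attached to this aim is about something narrower. In the Introduction, hypothesis (ii) is that women in the taekwondo (TKD) arm "have more favorable inter-individual responses (higher percentage of responders) in cognitive status" and in three further outcomes. The Conclusions carry the same bracketed explanation, and the Discussion speaks of "conducting a study comparing the group and inter-individual responses (responders vs. non-responders) in older women". The Simple Summary and Abstract drop the explanation; the Abstract predicts "greater inter-individual responses in cognitive status, brain activity, HRQoL, and postural balance than the others training methods".

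The method is in section 2.8.1: "The inter-individual variability of the intervention will be determined using previously reported criteria, and responders and non-responders will be classified" using the technical error, defined as "TE = SD (standard deviation) dif/√2". A woman whose beneficial change does not exceed 2 × TE is a non-responder, and Fisher's exact test compares the groups. No other procedure is tied to this aim. Section 2.8 plans general descriptive dispersion measures, and Levene's test beside the Shapiro-Wilk test. Neither is linked to change scores or to the variability of response.

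**The concern.** Variability of response is a statement about spread: how much the women in one arm differ from each other in what the training does for them. The proportion beyond a fixed cut-off is a different quantity. It moves when the whole arm shifts, even if every woman has the same true change, and it can stay still when the spread changes.

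The text uses variability, greater inter-individual responses and percentage of responders for what the one classification delivers. If the sentence in section 2.8.1 is followed literally, a difference in responder percentage would be reported as a difference in variability between training systems where there may be none. A real difference in spread could be missed, or could appear with the opposite sign. Hypotheses (i) and (ii) also cover the same four outcomes, so a TKD advantage in mean change would tend to support both.

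**Working it through.** **Inputs from the Protocol article.** TE is the SD of the difference between two repeated measurements divided by √2 (2.8.1), so the error SD of a change is √2 TE = 1.41 TE. The cut-off is a beneficial change above 2 TE (2.8.1). There are 16 women per arm, with 15% expected loss (2.3).

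**Assumptions, not in the document.** Changes are normal, TE is known exactly, and there is no drift or practice effect. The arm mean change *m* runs from 0 to 3 TE. The SD of true individual response *s* runs from 0 to 2 TE and is independent of measurement error.

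**Formula, in TE units.** The observed change has SD √(2 + s²), so

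responder share = 1 − Φ((2 − m)/√(2 + s²)).

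**The plan's own figure.** Section 2.8.1 attaches odds of 12 to 1 to the 2 TE cut-off. With m = 0 and s = 0, the probability of a change below 2 TE is Φ(2/1.414) = 0.9214, and the odds are 0.92135/0.07865 = 11.7 to 1. The figure reproduces, so this model agrees with the one behind the cut-off.

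**Responder share by mean and spread.**

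| Mean change (TE) | s = 0 | s = 1 TE | s = 2 TE |
|---|---|---|---|
| 0 | 7.9% | 12.4% | 20.7% |
| 1 | 24.0% | 28.2% | 34.2% |
| 2 | 50.0% | 50.0% | 50.0% |
| 3 | 76.0% | 71.8% | 65.8% |

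Two cells worked: for m = 1, s = 0, (2 − 1)/1.414 = 0.707 and 1 − Φ(0.707) = 0.240. For m = 3, s = 2, (2 − 3)/√6 = −0.408 and 1 − Φ(−0.408) = 0.658.

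- Down the s = 0 column there is no individual variation at all, yet the share runs from 7.9% to 76%.
- Along the rows, more spread raises the share when the mean is below the cut-off, leaves it unchanged at the cut-off, and lowers it above.
- The same share can come from opposite situations. With m = 0 and s = 2.45, √(2 + 6) = 2.83 and 2/2.83 = 0.707, which gives 24%, the same as m = 1 with no individual variation.

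**What Fisher's test would do** (exact enumeration, 16 per arm, two-sided 5%):

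- Means of 1 and 3 TE, no individual variation in either arm (24% v 76%): rejects with probability 0.78.
- Both means at 2 TE, s = 0 v s = 2 TE (50% v 50%): rejects with probability 0.02.
- Both means at 1 TE (24% v 34%) or both at 3 TE (76% v 66%), s = 0 v s = 2 TE: rejects with probability 0.04.

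**Precision of a direct measure.** After 15% loss, 16 × 0.85 = 13.6, taken as 14 women per arm. The 97.5% point of F with 13 and 13 df is 3.115. Its square root is 1.76, with reciprocal 0.57. The 95% CI of an SD ratio therefore runs from 0.57 to 1.76 times the estimate.

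**The case against.** The strongest answer is that the protocol says what it means. The Introduction, Discussion and Conclusions all explain inter-individual response as the percentage of responders, or responders against non-responders. Under that reading Fisher's test addresses hypothesis (ii) directly. This stands: a reader might infer that the secondary aim cannot be answered at all, and the document does not support that. Hypothesis (ii) needs no rewording, and the planned pre and post assessments in four arms, including an untreated control, already allow spread to be compared.

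A reader might also infer that the responder comparison only repeats the mean comparison of hypothesis (i). That is too strong as well. The share mixes mean and spread: at a mean of 0 it rises from 7.9% to 20.7% as *s* goes from 0 to 2 TE. The objection to the measure is that it cannot separate the two.

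Three further points have weight. The previously reported criteria lie in cited sources that are not at hand, so the absence of a spread measure is judged on the article's text. The means and SDs in the table are illustrative. An SD ratio from about 14 women per arm is imprecise, and it does not suit the MEFO, which section 2.7.1 describes as sorting women into three levels.

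None of this removes the mismatch. Section 2.8.1 itself uses the word variability for what the classification determines, and the Simple Summary and Abstract predict greater inter-individual responses without the explanation. The protocol has fixed a method for a named quantity, and the method does not measure it.

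**Conclusion.** The point holds as a mismatch between a stated aim and its measure. The share beyond 2 × TE is a valid analysis of responder proportion for hypothesis (ii), but it does not identify the variability of the inter-individual response. With no true individual variation, the share alone could differ by 52 percentage points between arms with means of 1 and 3 TE (76% − 24%). Raising the individual-response SD from 0 to 2 TE changes the share by +13 points at mean 0 (20.7% − 7.9%), +10 at mean 1, nothing at mean 2 and −10 at mean 3.

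These sizes rest on normal changes, a known TE and assumed means and SDs. The dependence on both mean and spread does not rest on the particular values, and better estimation of TE would not cure it. The equality at exactly 2 TE is a special case of the normal model. The comparison of mean effects is untouched, but an aim stated in the Abstract and Conclusions is affected, so the text should be corrected before results are reported.

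**What to change.** In section 2.8.1:

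- For continuous outcomes, add the SD of the 16-week change by arm, and the SD ratios of each trained arm to control and of TKD to multi-component training and to walking, with 95% CI. Label them exploratory. Do not apply them to the three-level MEFO classification.
- Keep the 2 × TE percentage and Fisher's test, named as the analysis of responder proportion for hypothesis (ii).
- Change the sentence that says variability is determined by the classification, and the unexplained wording in the Simple Summary and Abstract, so that no claim on variability rests on that percentage.

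If no measure of spread is added, rewording the aim as a comparison of the proportion of responders, wherever it appears, is enough to resolve the mismatch.

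The cost is a few sentences and, for the first option, a few lines of analysis on data already planned. The price of that option is low precision: with intervals of 0.57 to 1.76 times the estimate, only large differences in spread would show.
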